### Study population

Pregnant women who voluntarily participate in the prenatal education course offered by Fondazione Policlinico Agostino Gemelli IRCCS, Rome.

*Inclusion criteria:*

a) Nulliparous women.b) Willingness to participate in the preparation training program on pushing techniques.c) Singleton pregnancy.d) Age 18 years or older.e) Ability to understand and provide informed consent in Italian.f) Plan to deliver at the Fondazione Policlinico Agostino Gemelli IRCCS.

*Exclusion criteria:*

a) Multifetal (e.g., twins, triplets) pregnancies.b) Known obstetric complications or conditions that contraindicate a vaginal delivery (e.g., placenta previa).c) Medical or psychiatric conditions that would prevent participation in the educational program or adherence to study protocols.d) History of pelvic floor surgery or severe pelvic floor dysfunction that might affect participation or outcomes.e) Inability to understand study requirements or provide informed consent.f) Participants already enrolled in conflicting clinical trials or interventions that could influence the study’s outcomes.

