To quantify the proportion of women who demonstrate levator ani muscle (LAM) co-activation—defined as an anteroposterior diameter change (APD) < 0 mm—at two time-points: (i) during the TPUS-guided training session, and (ii) at birth, where an intrapartum sonographic assessment is feasible within routine clinical care.To compare postpartum maternal satisfaction between the control and TPUS-guided intervention arms, as measured by the Childbirth Experience Questionnaire 2 (score range 0–100).To quantify the difference of prevalence in 1st-, 2nd-, 3rd- and 4th-degree perineal tears between the control and the TPUS-guided intervention arms.To measure the difference in total postpartum blood loss (mL) within 24 hours of delivery between the control and the TPUS-guided intervention arms.To compare the rates of spontaneous vaginal birth, operative vaginal birth and unplanned caesarean sections between the control and the TPUS-guided intervention arms.To evaluate the prevalence of stress or urge urinary incontinence at 6, 12, 16 weeks postpartum between the control and the TPUS-guided intervention arms, defined as an International Consultation on Incontinence Questionnaire-Urinary Incontinence Short Form (ICIQ-SF) score ≥ 6.To compare the proportion of women that require pharmacological augmentation during the active second-stage of labour between the control and TPUS-guided intervention arms.To quantify the association between persistent fetal malposition (non-occiput-anterior at full cervical dilatation and/or at delivery) and the length of the second stage of labour (minutes), and to test whether this association differs between the control and TPUS-guided intervention arms. This association is observational in nature and is not interpreted as a randomised comparison.

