### Study procedures

Study procedures are summarized in Fig 2. Pregnant women between 28 + 0 and 37 + 0 weeks of gestation who participate in the antenatal preparation course sponsored by the Fondazione Policlinico Agostino Gemelli IRCCS will be informed about this study. The antenatal preparation course is held monthly, and it encompass nearly 60 women per course. Women who express interest will be scheduled for an in-person appointment with a research midwife, during which they will undergo eligibility screening. Those meeting the inclusion criteria and providing written informed consent will be randomized into one of two groups:

Midwife-led TPUS-guided pushing training group.Midwife-led pushing training only group (control).

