### Data collections

Data will be collected at multiple time points throughout the study to ensure comprehensive evaluation of the interventions’ effectiveness and safety (Fig 1). At enrolment, baseline demographic and obstetric information, including maternal age, parity, medical history, and pregnancy details, will be recorded. During the intervention period, attendance and engagement with both the online educational video and in-person sessions will be tracked. For participants in the TPUS-guided arm, detailed observations and measurements captured through TPUS will be documented during practical exercises to assess technique and muscle engagement.

Delivery outcomes will be extracted from medical records, including mode of birth (vaginal or caesarean section), duration of second stage of labour, incidence of any degree perineal tears, and any complications. Following childbirth, women’s satisfaction with the delivery experience will be evaluated using validated questionnaires. Women will be contacted at 6, 12 and 16 weeks post-partum. At each time point, urinary incontinence will be assessed using the ICIQ-SF questionnaire. At the 16 weeks follow-up, women will additionally be asked whether they have attended pelvic floor rehabilitation sessions since delivery. Collected data will be handled using a secure, de-identified database, with regular checks to ensure data integrity and adherence to ethical guidelines. Pseudonymized datasets will be stored on Zenodo (https://zenodo.org/), a secure open-access platform compliant with EU data protection regulations and FAIR principles.

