The primary endpoint will be analysed using multivariable linear regression, with treatment arm as the main predictor. The model will be adjusted for pre-specified baseline covariates only, that is, variables measured before randomisation: maternal age, body mass index at enrolment, gestational age at randomisation, maternal height, and sonographic estimated fetal weight at the last available third-trimester scan. Consistent with ICH E9, no post-randomisation variable is included in the confirmatory model, since conditioning on variables measured after allocation may invalidate the randomisation-based causal interpretation of the treatment effect. This applies in particular to fetal head position at full cervical dilatation, epidural analgesia and gestational age at delivery, which are potential intermediate variables on the causal pathway between the intervention and the primary endpoint. Their distribution across arms will be reported descriptively, and epidural analgesia and fetal head position will be examined as potential effect modifiers through interaction terms, as exploratory analyses. The primary result will be reported as an adjusted mean difference with 95% confidence interval; the p-value will be provided as secondary inferential information. If the residuals of the linear model indicate substantial departure from normality, a bootstrap confidence interval will be computed. Women who do not reach the active second stage (e.g., caesarean delivery before full dilatation) will not contribute to the primary analysis but will be retained in the ITT population for all secondary outcomes. For clarity, the primary estimand may therefore be summarised as the difference in adjusted mean duration of the active pushing phase between arms among randomised nulliparous women reaching the active second stage, with operative vaginal delivery and second-stage caesarean section handled under a treatment-policy strategy as delivery events at the observed time. The number of women contributing to each analysis, with the corresponding denominators and reasons for non-contribution, will be reported by arm in the CONSORT flow diagram, and the baseline characteristics of women not reaching the active second stage will be compared between arms using standardised mean differences. Sensitivity analyses will include multiple imputation under the missing-at-random assumption and inverse probability weighting to assess the robustness of the primary estimate to differential attrition, applied to observations that are missing rather than undefined, such as incomplete partogram times or non-returned questionnaires; where an imbalance is observed in the proportion of women reaching the active second stage, inverse probability of selection weights will be applied accordingly. Time to spontaneous vaginal birth from the onset of active pushing will additionally be described using cumulative incidence functions, with operative vaginal delivery and second-stage caesarean section treated as competing events rather than as censored observations, and compared between arms using Gray's test. This analysis is supportive and exploratory.

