
Mode of delivery (spontaneous vaginal birth vs. operative vaginal or caesarean), perineal tears (≥ 3rd degree vs. none/1st–2nd degree), postpartum haemorrhage (≥ 500 mL vs. < 500 mL), and need for pharmacological augmentation during the active second stage will be analysed using logistic regression with the same set of pre-specified baseline covariates. Results will be reported as adjusted odds ratios with 95% CIs, accompanied by absolute risks and risk differences by arm to facilitate clinical interpretation. For endpoints with a low expected number of events, Firth's penalised-likelihood estimation will be used. Third- and fourth-degree perineal tears will be analysed among all women reaching the second stage, with caesarean deliveries counted as no injury, and additionally among women delivering vaginally. Mode of delivery is also addressed within the competing-risks analysis described above. Total postpartum blood loss (mL) and maternal satisfaction (CEQ-2 score) will be analysed using multivariable linear regression as described for the primary endpoint, reporting adjusted mean differences with 95% CIs, with bootstrap confidence intervals reported for blood loss in view of its expected skewness. Urinary incontinence (ICIQ-SF score ≥ 6) will be assessed at 6 weeks, 12 weeks and16 weeks postpartum. The outcome will be modelled using mixed-effects logistic regression with a random intercept for participant and fixed effects for treatment arm, time point, and their interaction, adjusted for the same baseline covariates. This approach accounts for within-subject correlation across repeated assessments and allows estimation of the treatment effect trajectory over time and makes use of all available observations under a missing-at-random assumption. Both the interaction term and the adjusted treatment effect at each time point will be reported. Attendance at postpartum pelvic floor rehabilitation, a post-randomisation variable, will be summarised descriptively by arm and, where uptake exceeds 10% in either arm, included in sensitivity analyses for pelvic floor–related outcomes as described above. Pre-specified subgroup analyses will examine potential effect modification by: (i) Within-arm analysis of levator ani function (intervention arm only); (ii) gestational age at intervention (28–34 weeks vs. 35–37 weeks); and (iii) epidural analgesia (yes/no). Subgroup (ii) and subgorup (iii) are defined by post-randomisation variables and are reported as exploratory only. Subgroup effects will be estimated via interaction terms in the regression models and reported as stratum-specific effect estimates with 95% CIs. All secondary, subgroup, and repeated-measures analyses are regarded as exploratory and hypothesis-generating. The trial is powered exclusively on the primary endpoint. Results of secondary analyses will be reported as point estimates with 95% confidence intervals without correction for multiplicity and should be interpreted in the context of the overall pattern of findings rather than as confirmatory evidence. All analyses will be conducted using R (R Foundation for Statistical Computing) and STATA (StataCorp LLC).

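### The urinary incontinence model has no pre-randomisation continence measure, although women already leaking in pregnancy are eligible: a minor loss of precision and interpretability for one exploratory endpoint

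*Protocol article*

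**What the plan says.** **Who can enter.** Under Study population, the only criterion on pelvic floor status is exclusion (d): "History of pelvic floor surgery or severe pelvic floor dysfunction that might affect participation or outcomes". No continence threshold is set. Under Study procedures, recruitment is of "Pregnant women between 28 + 0 and 37 + 0 weeks of gestation who participate in the antenatal preparation course".

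**What the outcome is.** The secondary objectives include "To evaluate the prevalence of stress or urge urinary incontinence at 6, 12, 16 weeks postpartum", with a case defined as an ICIQ-SF score of 6 or more.

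**When it is measured.** Data collections states: "Women will be contacted at 6, 12 and 16 weeks post-partum. At each time point, urinary incontinence will be assessed using the ICIQ-SF questionnaire". For baseline, the same section says: "At enrolment, baseline demographic and obstetric information, including maternal age, parity, medical history, and pregnancy details, will be recorded". No continence item is named there. Timing is also referred to Fig 1, which is not shown in the text available to us.

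**How it is analysed.** The Statistical analysis plan section specifies a mixed-effects logistic model with a participant random intercept and "fixed effects for treatment arm, time point, and their interaction, adjusted for the same baseline covariates". Those covariates are the ones listed for the primary endpoint: "maternal age, body mass index at enrolment, gestational age at randomisation, maternal height, and sonographic estimated fetal weight at the last available third-trimester scan". The only pelvic-floor variable considered for adjustment is attendance at postpartum rehabilitation, which is measured after randomisation and enters sensitivity analyses only.

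**The concern.** Late-pregnancy leakage short of severe dysfunction is compatible with entry. A woman who would score 6 or more before training and still does so at 6 weeks counts as a case in the same way as a woman whose incontinence began with the birth. The covariates were chosen for the length of pushing and carried over to a continence outcome without the one baseline variable that measures the same thing.

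Three things follow:

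- The arm comparison is less precise than it could be.
- If pre-existing incontinence happens to differ between arms, the model has no term with which to correct for it.
- The trial cannot say whether a difference reflects fewer new cases or more recovery among existing ones. The Expected results section presents protection of the pelvic floor as a hoped-for benefit, so readers will want that distinction.

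**Working it through.** **The plan's own figures.** The plan states no rate, effect or power for incontinence. The only sized endpoint is pushing duration. With a 20-minute difference and SD 53.5, n per arm = 2(1.96 + 0.8416)² × 53.5²/20² = 112.3, so 113. With d = 0.37 it is 2(1.96 + 0.8416)²/0.37² = 114.7, so 115. The stated figure is 114. Inflation gives 228/0.85 = 268.2, against 268 stated. These figures reproduce, and nothing below alters them.

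**Inputs for incontinence (all assumed).** Let b be the proportion scoring 6 or more before randomisation, p₁ the postpartum risk in those women, and p₀ the risk in the others. Assumed ranges: b 15-35%, p₁ 50-60%, p₀ 10-12%.

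**Share of postpartum cases that pre-exist.** Overall risk = b·p₁ + (1 − b)·p₀, and share = b·p₁ / overall.

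| b, p₁, p₀ | Overall risk | Share pre-existing |
|---|---|---|
| 0.15, 0.50, 0.12 | 0.075 + 0.102 = 0.177 | 42% |
| 0.25, 0.50, 0.12 | 0.125 + 0.090 = 0.215 | 58% |
| 0.25, 0.60, 0.10 | 0.150 + 0.075 = 0.225 | 67% |
| 0.35, 0.50, 0.10 | 0.175 + 0.065 = 0.240 | 73% |

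These are four combinations, not every corner of the ranges. At 0.35, 0.60, 0.10 the share is 0.210/0.275 = 76%.

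**Outcome variance explained by baseline status.** R² = b(1 − b)(p₁ − p₀)² / [overall(1 − overall)]. In row order this gives 0.126, 0.160, 0.269 and 0.200. It indicates how informative the covariate is. Turning it into an effective sample size through 1/(1 − R²) is a linear-model device, and the planned model is logistic, so the power figures below are the better guide.

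**Power.** The simulation used one binary outcome at a single visit, 120 women per arm, a conditional odds ratio of 0.5 and 2,000 runs per row.

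| Row | Unadjusted | Adjusted | Gain (points) |
|---|---|---|---|
| 1 | 0.34 | 0.37 | 3 |
| 2 | 0.39 | 0.43 | 4 |
| 3 | 0.32 | 0.40 | 8 |
| 4 | 0.40 | 0.47 | 7 |

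A repeat with 1,500 runs gave gains of 3, 5, 10 and 8. Each simulated power has a standard error of about √(0.4 × 0.6/2000) = 0.011, so roughly 3-8 points is a fair summary. It is not a calculation for the planned three-visit mixed model.

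**Chance imbalance.** At 134 per arm the between-arm difference in b has SD √[2b(1 − b)/134]. This is 4.4 percentage points at b = 0.15, 5.3 at 0.25 and 5.8 at 0.35. At b = 0.25, a one-SD imbalance moves the postpartum contrast by 0.053 × (p₁ − p₀), that is 0.053 × 0.38 = 2.0 points to 0.053 × 0.50 = 2.6 points.

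**New versus persistent cases.** This illustration needs a further assumption: training halves new onset and does nothing for existing incontinence. With b 10-40%, persistence 40-60% and new onset 15%, a risk ratio of 0.50 among women continent at baseline appears among all women as between 0.1075/0.175 = 0.61 and 0.285/0.330 = 0.86. A covariate does not undo this. A separate report for women below 6 at baseline does.

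**How many women could still give a baseline score.** Enrolment runs from 18 July 2025 to 31 July 2026, 378 days. The Setting section reports 2025 hospital rates as already recorded, so the text dates from after the end of that year, at least 166 days in: 166/378 = 44%. If accrual was even and the gain is roughly proportional to the share with a score, 0.56 × 3 to 0.56 × 8 leaves about 2-4 points at best.

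**The case against.** The case against is substantial, and most of it limits the size of the point.

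- **Bias.** A reader might infer that pre-existing cases bias the comparison. The documents do not support that. Allocation is randomised 1:1, so continence status is balanced in expectation, and chance imbalance is part of what the 95% confidence interval already covers. What remains is a wider interval than necessary.
- **A wrong endpoint.** A reader might infer that counting these women as cases is an error. The objective is worded as prevalence, so a woman scoring 6 or more at 6 weeks is a case whatever her history. The limit is on interpretation as childbirth-related incontinence.
- **No baseline score at all.** A reader might infer that none is taken. The text names none, but Fig 1 is not shown, the baseline list is open-ended, and an article may condense the full protocol. What can be confirmed is that the stated covariate set contains no continence variable.
- **Status of the endpoint.** All secondary analyses are declared exploratory, and the trial is powered only on the primary endpoint. In the simulation above, power stays below one half with or without adjustment.
- **The size.** Every rate is assumed, and the simulation is simpler than the planned model.

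All of this stands. It does not remove the point. The covariate list for this outcome is explicitly fixed, the plan itself prefers variables measured before randomisation, and an exploratory comparison read through its confidence intervals benefits from cheap precision. The random intercept handles correlation between visits and does not replace a baseline measure.

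**Conclusion.** The point holds as a minor one. The incontinence model as stated omits pre-randomisation continence status in a population where leakage short of severe dysfunction is allowed. The consequences are some lost precision, no correction for a chance imbalance, and no separation of new from persistent incontinence.

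Under the assumed rates, 42-73% of postpartum cases in the four combinations would pre-exist, and full adjustment would be worth roughly 3-8 points of power in a single-visit approximation. The documents supply none of these rates, so the figures show plausible size only. There is no systematic bias, no fault in the eligibility rule, and no effect on the primary analysis or its sample size.

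**What to change.** 1. Check the Fig 1 schedule. If it does not already include a baseline ICIQ-SF, give the questionnaire at the existing in-person screening visit, before randomisation, to all women still to be enrolled.
2. Add the baseline score to the mixed-effects logistic model for incontinence, with a missing-indicator term for women enrolled before the change. Whether the score is missing then depends on enrolment date and not on arm, so the indicator is acceptable here.
3. Report incontinence among women scoring below 6 at baseline as a supportive analysis. The subgroup is defined before randomisation, so the comparison within it remains randomised.
4. Leave exclusion (d) unchanged, and do not turn the history taken for it into a covariate. Every enrolled woman has passed that criterion, so it would be constant, and the article does not say that milder leakage is recorded at screening.

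The cost is one short questionnaire at a visit that already takes place, two model terms and a protocol amendment. The downside is that women already enrolled will have no score, possibly a large share, so the gain is partial. A pre-randomisation score cannot be recovered later, so the benefit shrinks as enrolment proceeds.

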#### Setting.

This single-center study will be conducted at Fondazione Policlinico Universitario Agostino Gemelli IRCCS Rome, an academic private tertiary-level hospital located in central Italy, with over 4,000 births per year. Childbirth care is characterised by continuous one-to-one intrapartum support provided by registered midwives under the supervision of senior midwives and obstetricians. Second-stage management follows physiological principles. In nulliparous women with epidural analgesia, delayed pushing is practised until the urge to push is felt or the fetal head reaches the pelvic floor; active pushing is then maternal-led, with verbal coaching by attending midwives. Practitioners do not routinely use ultrasound during the pushing stage to assess fetal station or perineal status. Intrapartum care is identical for both study arms; only the antenatal training component differs. In 2025 the hospital recorded an epidural analgesia rate of 72%, a primary cesarean section rate of 19%, and an operative vaginal delivery rate of approximately 11%, performed by vacuum extraction (Kiwi Cup).

Although a dedicated pelvic floor outpatient unit is available, no standardized postpartum pelvic floor rehabilitation protocol is in place. Rehabilitation sessions are therefore not scheduled as part of routine care, and attendance at external pelvic floor rehabilitation is not systematically recorded. All women are nonetheless advised at discharge of the importance of pelvic floor evaluation in the postpartum period. Attendance at pelvic floor rehabilitation will be recorded at the16 weeks follow-up contact. Should the rate of rehabilitation uptake exceed 10% in either arm, it will be included as a covariate in exploratory sensitivity analyses for pelvic-floor related outcomes.

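### Two exploratory analyses condition on post-randomisation variables where this is avoidable: rehabilitation attendance as a covariate, and gestational age at intervention as a subgroup

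*Protocol article*

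**What the plan says.** **Rehabilitation covariate.** The Setting section states: "Should the rate of rehabilitation uptake exceed 10% in either arm, it will be included as a covariate in exploratory sensitivity analyses" for pelvic-floor outcomes. The Statistical analysis plan section repeats the rule and classifies the variable: "Attendance at postpartum pelvic floor rehabilitation, a post-randomisation variable, will be summarised descriptively by arm", with the same 10% trigger for entering it into sensitivity analyses.

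**Timing.** Under Data collections, at the 16-week contact "women will additionally be asked whether they have attended pelvic floor rehabilitation sessions since delivery". The outcome has three visits: "Urinary incontinence (ICIQ-SF score ≥ 6) will be assessed at 6 weeks, 12 weeks and16 weeks postpartum". It is analysed in one mixed-effects logistic model adjusted for baseline covariates.

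**Subgroup (ii).** The Statistical analysis plan section splits women by gestational age at intervention (28–34 vs 35–37 weeks). It says that this subgroup and the epidural subgroup "are defined by post-randomisation variables and are reported as exploratory only". The same section lists gestational age at randomisation among the baseline covariates of the primary model.

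**The general principle.** For the primary endpoint, "no post-randomisation variable is included in the confirmatory model", because "conditioning on variables measured after allocation may invalidate the randomisation-based causal interpretation of the treatment effect".

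**The concern.** A sensitivity analysis is read as a test of whether the main estimate survives a change of assumptions. Adjusting for a variable that arises after allocation, and possibly after the outcome, changes the question being asked. If the adjusted and unadjusted incontinence results differ, the reader cannot tell whether the main result is fragile or the adjustment has introduced bias.

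The article describes rehabilitation as unscheduled and without a standard local protocol, so attendance is self-selected. It is plausible that women who leak attend more often. It is also possible that women who have watched their pelvic floor on ultrasound attend more often. If both are true, conditioning on attendance links arm and outcome even when training has no effect on continence.

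For the subgroup, the stake is smaller. A split on a baseline variable keeps the randomised comparison within each stratum and is defined for every randomised woman. A split on timing of the intervention leaves a woman who never attends the session without a value.

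**Working it through.** **1. Order of measurement (needs no assumed rates).**

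| Item | When | Article section |
|---|---|---|
| Incontinence | 6, 12 and 16 weeks | Data collections; Statistical analysis plan |
| Attendance, any since delivery | asked once, at 16 weeks | Setting; Data collections |

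A woman who leaks at 6 weeks and first attends at week 10 counts as an attender in the model for her 6-week outcome. The covariate then describes an event after the outcome, and a single question about the whole period cannot place attendance before or after a given visit. In addition, a woman not reached at 16 weeks has no attendance value even if she answered at 6 and 12 weeks. Unless that value is imputed, the adjusted model loses her earlier observations.

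**2. Illustration with no true effect (all rates assumed).** The documents give no incontinence or attendance rates. Let Y = 1 for leaking, A = 1 for the ultrasound arm and R = 1 for attendance. Assume 25% leak in both arms, so the true odds ratio is 1.00, and P(R = 1 | Y, A) = expit(a + bY + gA). Write P_YA for this probability. By Bayes' rule, the odds ratio of Y on A among attenders is

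OR = (P11 × P00) / (P10 × P01).

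The same formula with 1 − P in place of P gives the odds ratio among non-attenders. The two are equal because the attendance model has no interaction term.

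| a, b, g | P00 | P10 | P01 | P11 | Adjusted OR | Uptake control / ultrasound |
|---|---|---|---|---|---|---|
| −2.2, 1.8, 0.8 | 0.0998 | 0.4013 | 0.1978 | 0.5987 | 0.75 | 17.5% / 29.8% |
| −2.2, 1.4, 0.8 | 0.0998 | 0.3100 | 0.1978 | 0.5000 | 0.81 | 15.2% / 27.3% |
| −2.2, 1.4, 0.5 | 0.0998 | 0.3100 | 0.1545 | 0.4256 | 0.89 | 15.2% / 22.2% |
| −2.2, 1.8 or 1.4, 0 | 0.0998 | 0.4013 or 0.3100 | = P00 | = P10 | 1.00 | equal in both arms |

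First row: 0.5987 × 0.0998 / (0.4013 × 0.1978) = 0.75. Uptake is 0.25 × 0.4013 + 0.75 × 0.0998 = 17.5% in controls and 0.25 × 0.5987 + 0.75 × 0.1978 = 29.8% in the ultrasound arm. In the last row arm does not affect attendance and the bias is nil, yet uptake is above 10% and the trigger still fires. The trigger therefore does not separate harmful from harmless adjustment.

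**3. Illustration with a true effect and no direct effect of arm on attendance (also assumed).** Take leaking at 30% in controls and 20% with ultrasound training. The true risk difference is −10.0 points and the odds ratio is (0.20/0.80)/(0.30/0.70) = 0.58. Let attendance depend on leaking only. In a linear model with attendance added, the difference becomes −8.8 points (attendance 30% in leakers vs 5% in others), −7.2 (50% vs 5%) or −5.3 (70% vs 5%). The odds ratio stays at 0.58. In a separate simulation where attendance follows underlying severity, an odds ratio of about 0.59 moves to between 0.59 and 0.65. The planned model is logistic, so under this mechanism the shift in its reported measure ranges from none to modest.

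**4. Subgroup (ii).** Gestational age at randomisation is already needed for the primary model, so the baseline version of the split requires no new data. The interval between randomisation and training is not stated, so the number of women who would change stratum cannot be computed.

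**The case against.** A reader might infer that the plan breaks its own rule. It does not. The bar covers the confirmatory model for the primary endpoint, and the same section openly allows exploratory interactions with epidural analgesia and fetal head position. Both analyses discussed here are labelled post-randomisation and exploratory, and the main incontinence model uses baseline covariates only. That stands: there is no contradiction, and the limitation is largely disclosed. The label does not, however, make the adjusted estimate interpretable.

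A reader might also take attendance to be a consequence of leaking. The article does not say so. All women are advised at discharge about pelvic floor evaluation, and both arms receive teaching on the levator ani. Selection by symptoms is a reasonable inference and no more.

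The odds ratios of 0.75 to 0.89 rest wholly on assumed inputs and on one binary outcome rather than the three-visit model. With 25% incontinence and 134 women per arm, the standard error of the log odds ratio is √[2 × (1/33.5 + 1/100.5)] = 0.28. The illustrated biases of 0.12 to 0.29 on the log scale are therefore at most about one standard error.

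Rehabilitation is a plausible co-intervention, and one could keep the analysis with a caveat or restrict it to 16 weeks. Restriction would remove the clearest timing fault, but attendance would still be a self-selected variable arising after allocation.

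On subgroup (ii), both arms attend training, so the variable exists in both, and timing of training is a fair question. Any bias is probably small. The epidural and head-position analyses are post-randomisation too, but no baseline substitute exists for them, so they are not raised here.

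**Conclusion.** The point holds as a minor one about two exploratory analyses. The timing of the attendance question, read from the article alone, is enough to show that the rehabilitation-adjusted estimate cannot test the robustness of the randomised effect at 6 and 12 weeks. The reason the plan gives for keeping such variables out of its primary model applies equally, although the rule itself does not extend this far.

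The direction and size of any bias cannot be fixed from the documents. On the odds-ratio scale with no true effect, it runs from nil, if arm does not affect attendance, to 0.75 in the most adverse scenario shown. Subgroup (ii) gives up a baseline definition for no evident gain, with probably small consequences. The primary analysis, alpha, 114 women per arm and the enrolment target of 268 are unaffected.

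**What to change.** 1. In Setting and in Statistical analysis plan, delete the rule that adds rehabilitation attendance as a covariate above 10% uptake. Keep the descriptive table of attendance by arm, and state that the baseline-adjusted mixed model gives the only treatment-effect estimate for incontinence.
2. Define subgroup (ii) by gestational age at randomisation, with the same split of 28–34 vs 35–37 weeks, and remove it from the sentence listing subgroups defined by post-randomisation variables. Epidural analgesia stays in that sentence.

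Both changes are to wording only. No new data, visits or participants are needed.
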